## Abstract

**Background:**

Pain and postoperative nausea and vomiting (PONV) are the most prevalent postoperative complications following orthognathic procedures. Acupuncture therapy is advocated as one of the treatment alternatives for preventing PONV. This trial aims to investigate the efficacy of preoperative intradermal acupuncture in combination with dexamethasone and palonosetron in high-risk patients undergoing bimaxillary orthognathic surgery, employing a multimodal risk-reduction strategy aligned with consensus guidelines.

**Methods:**

This single-center, double-blind, randomized controlled trial will enroll 216 participants allocated to two groups: group A, the acupoint stimulation group and group B, the sham stimulation group. All subjects will receive standardized PONV prophylaxis including dexamethasone 5 mg IV, palonosetron 0.075 mg IV, target-controlled propofol infusion (0.5 μg/mL), and laryngeal packing following anesthesia induction. Patients in both groups receive two sterile thumb-tack needles – one real needle and one identical-appearing sham needle without a pointed tip. In group A, the real needles are placed at the PC6 acupoint, and the sham needles are placed at the sham acupoint on the forearm. In group B, the real needles are placed at the sham acupoint, while the sham needles are placed on the PC6 acupoint. Finally, all patients will have the sterile opaque patches applied to each acupoint for allocation concealment. The needles will remain in place up to 24 h postoperatively at least. The primary outcome will be the incidence of PONV at 24 h postoperatively. Secondary outcomes will include the incidence rates of PONV at different postoperative intervals and a 15-point quality of life recovery score at 24 h postoperatively.

**Discussion:**

Despite dual-mechanism pharmacological prophylaxis, orthognathic surgery patients exhibit persistent postoperative nausea rates approaching 50%. It is necessary to introduce a third combined measure to prevent PONV. This trial aims to investigate a novel triple-modality prophylactic strategy for PONV mitigation in bimaxillary orthognathic procedures.

**Systematic review registration:**

https://itmctr.ccebtcm.org.cn/mgt/project/view/1966089260633292800, Identifier ITMCTR2025001713.

## Background

Orthognathic surgery can effectively address malocclusion and optimize facial symmetry aesthetics, occlusal patterns, and temporomandibular joint dynamics through three-dimensional correction of malocclusions of the jaw and face. With the increasing demand for psychosocial well-being enhancement, particularly in social interaction domains, more and more candidates pursue bimaxillary surgery (1). The most common postoperative complications of orthognathic surgery are pain and PONV. Severe PONV exerts a stronger impact on early postoperative recovery than moderate pain. PONV is a significant factor affecting overall perioperative satisfaction (2). PONV can lead to gastrointestinal reactions, electrolyte and acid–base imbalances, and in severe cases, may result in wound dehiscence, sudden increases in blood pressure and intracranial pressure, and aspiration pneumonia (3). In bimaxillary patients, mouth opening is limited due to elastic steel wire fixation, external bandage fixation, and facial swelling. PONV may cause fatal aspiration (4).

Female gender, younger age, non-smokers, a history of motion sickness, laparoscopic surgery, inhalation anesthesia administration, and high-dose opioid utilization constitute well-established independent predictors of PONV (5). The incidence of PONV in general surgical populations approximates 30%, while it can be as high as about 60% in orthognathic surgery patients, despite routine use of dexamethasone and 5-HT3 antagonists for prevention (6–8). Intraoperative controlled hypotension, rapid palatal expansion, elastic traction between the upper and lower jaws, intermaxillary fixation wires, and blood ingestion postoperatively are independent risk factors that distinguish orthognathic surgery from other general surgical procedures (9–11). Notably, bimaxillary osteotomy emerges as the most significant predictor of PONV development, necessitating distinct prophylactic strategies compared with general surgical procedures. Although the consensus guidelines recommend using propofol for induction/maintenance as strategies to reduce baseline PONV risk, current evidence suggests total intravenous anesthesia (TIVA) demonstrates may not fully address delayed PONV in orthognathic settings, potentially attributable to the temporal pattern of PONV manifestation (12). Whereas inhalational agent-induced emesis predominantly occurs within the immediate postoperative phase (0–2 h) (13), maxillofacial surgery patients exhibit 2.7-fold higher PONV incidence during the delayed recovery window (2–24 h postoperatively) (14).

For the aforementioned high-risk factors, various antiemetic regimens with multimodal pharmacological interventions targeting distinct pathophysiological pathways are currently incorporated in orthognathic surgery, such as serotonin 3 (5-HT3) receptor antagonists, glucocorticoids, opioid-sparing analgesic protocols, nasogastric decompression, and throat packs. These interventions exhibit distinct pharmacokinetic profiles, therapeutic efficacy, and adverse effect spectra, with no monotherapy demonstrating complete PONV prevention (15). Combination therapy is superior to monotherapy. In current anesthesia practice, dexamethasone combined with palonosetron, a second-generation 5-HT3 receptor antagonist with prolonged receptor-binding kinetics (mean elimination half-life: 40 h), constitutes the baseline dual antiemetic regimen for high-risk patients (16, 17). Acupuncture therapy is also endorsed as one of options for preventing PONV in the Fourth Consensus Guidelines for the Management of PONV in 2020 (3). Commonly used acupoints include the Neiguan point (PC6) on the pericardium meridian, the Zusanli point (ST36) on the stomach meridian, and the Hegu point (LI4) on the large intestine meridian. While the precise mechanism remains incompletely elucidated, it may involve modulating sympathetic nerve activity and gastrointestinal function, promoting potential gastrointestinal motility to prevent PONV.

Acupuncture has been well-documented in literatures on abdominal, gynecological, and otolaryngological surgery in PONV prophylaxis. Nevertheless, its application in orthognathic procedures remains limited. Existing acupuncture protocols predominantly involve intraoperative acupoint stimulation that terminates upon patient transfer from the operating theater. It is unclear whether acupuncture can offer comparable benefits in preventing PONV in orthognathic surgery patients, as it does in other abdominal surgeries. Current evidence derives primarily from trials comparing acupuncture monotherapy against single-agent pharmacotherapy, notably omitting guideline-recommended combination prophylaxis in control arms – a methodological limitation that reduces external validity and impedes clinical implementation (18–20).

Based on the risk minimization strategy, we evaluate the effect of preoperative intradermal acupuncture in PC6 point combined with dexamethasone and palonosetron in preventing PONV of the patients scheduled for bilateral orthognathic surgery, to verify the incremental antiemetic benefits of acupoint stimulation beyond routine PONV prevention strategies.

## Methods/design

### Study design

This trial is a single-center, prospective, randomized, double-blind, double-mimicry placebo-controlled trial, and will be conducted in Peking University Shenzhen Hospital from October 2025 to March 2028. The protocol has been approved by the Medical Ethics Committee of Peking University Shenzhen Hospital (approval number: 2025124) and registered at the ITMCTR (Trial registration number: ITMCTR2025001713).

### Subject evaluation, screening and recruitment process

A total of 216 patients scheduled for elective bilateral orthognathic surgery will be evaluated, screened, and sequentially recruited by the attending anesthesiologists one day prior to the surgical procedure. Eligible participants will be randomly assigned in a 1:1 ratio to either group A (acupoint stimulation group) or group B (sham stimulation group). Informed consent must be obtained from all participants before randomization. The study protocol flowchart is presented in Figure 1, while the detailed study schedule is summarized in Table 1.

**Figure 1 fig1:**
[figure not shown]
Protocol flow. PONV, postoperative nausea and vomiting; QoR-15 score, Quality of Recovery score; PCA, patient-controlled analgesia.

**Table 1 tab1:** Study schedule.

	Screening	Intervention	Operation	Recovery	Follow-up		
Time	The day before operation	Before induction	During surgery	Stay in the recovery room	0–2 h Postoperative	2-6 h Postoperative	6-24 h Postoperative
Eligibility screen	✓						
Informed consent	✓						
Demographic data	✓						
ASA status	✓						
Apfel score	✓						
Randomisation	✓						
PC6 stimulation		✓	✓	✓	✓	✓	✓
Duration of surgery			✓				
Duration of anesthesia			✓				
Duration of controlled hypotension			✓				
Consumption of narcotic drugs			✓				
Extubation time				✓			
NRS score right after extubation				✓			
Duration of PACU stay				✓			
Nausea				✓	✓	✓	✓
Vomiting				✓	✓	✓	✓
Numbers of PCA request							✓
Total PCA volume (mL) delivered							✓
QoR-15 assessment							✓

ASA status, American Society of Anesthesiologists status; NRS, Numerical Rating Scale; PACU, post-anesthesia care unit; PONV, postoperative nausea and vomiting; PCA, patient-controlled analgesia.

### Eligibility criteria

The inclusion criteria are defined as follows: (1) Patients scheduled for bilateral orthognathic surgery (including Le Fort I osteotomy and bilateral sagittal split osteotomy); (2) male and female patients aged 18 to 64 years; (3) American Society of Anesthesiologists (ASA) physical status I-II; (4) patients informed about the study protocol with signed written consent.

The exclusion criteria comprise: (1) Presence of local scars or infections in acupuncture areas; (2) limb absence or peripheral nerve injury; (3) body mass index (BMI) > 30 kg/m^2^; (4) history of substance abuse; (5) history of central nervous system disorders or psychiatric conditions; (6) requirement for postoperative intensive care unit (ICU) transfer; (7) current participation in other clinical trials.

Participants meeting any of the following criteria post-enrollment will be withdrawn: (1) Surgical cancellation or conversion to a single-jaw procedure; (2) inability to tolerate acupuncture therapy; (3) premature removal (<24 h) of thumb-tack needles for any reason. All withdrawal cases must be thoroughly documented. Participants who have received the intervention will complete follow-up assessments. No efficacy analyses will be performed for withdrawn cases.

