### Emergency unblinding

Following acupoint stimulation, immediate emergency intervention must be initiated if patients develop acute allergic reactions, severe bradycardia (heart rate <40 bpm), profound hypotension (systolic blood pressure <70 mmHg), acute respiratory distress, or cardiac arrest. Participants meeting these criteria will be immediately withdrawn from the trial. The principal investigator will disclose the allocation details to the treatment team and submit a formal report to the ethics committee after stabilization of the patient’s condition. The emergency unblinding procedure is detailed in Figure 2.

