### Sample size estimation

Based on existing literature (8), PONV incidence in the control group is estimated to be 61% (p_1_ = 0.610). We anticipate that by minimizing risk strategies and acupoint stimulation, we hypothesize a 30% relative reduction in PONV incidence following bilateral orthognathic surgery [p_2_ = p_1_ × (1–0.3) = 0.610 × 0.7 = 0.427]. The 2020 Fourth Consensus Guidelines for PONV established equivalent efficacy between PC6 acupoint stimulation and pharmacological prophylaxis regarding nausea control, vomiting reduction, and rescue antiemetic requirements. Therefore, this trial aims to assess the combinatorial effect of acupuncture, dexamethasone, and palonosetron on PONV incidence reduction in patients undergoing bilateral orthognathic surgery, using a two independent-sample superiority test for sample size calculation. A one-sided superiority test is employed, with a significance level *α* set at 0.05, and Zα being 1.645. The statistical power (confidence level) is 1-*β*, which is 0.8, and Zβ is 0.84. The sample size per group is calculated using the formula:

$$n=\frac{{\left(Z_{\alpha }\sqrt{2\bar{p}(1-\bar{p})}+Z_{\beta }\sqrt{p_{1}(1-p_{1})+p_{2}(1-p_{2})}\right)}^{2}}{{\left(p_{1}-p_{2}\right)}^{2}}$$

The derived minimum sample size per group is 92 (total *N* = 184). Accounting for 10% attrition and implementing stratified randomization with block size 4, the adjusted final enrollment target reaches 104 participants per group (total *N* = 208).

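### The only efficacy analysis leaves out participants withdrawn after randomisation (early needle removal, intolerance, single-jaw conversion), although treated participants are followed up; the direction and size of the resulting bias are unknown

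*Protocol article*

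**What the plan says.** The Eligibility criteria section lists three grounds for withdrawal after enrolment: cancellation of surgery or conversion to a single-jaw procedure; intolerance of the acupuncture; and "premature removal (<24 h) of thumb-tack needles for any reason". Two sentences then settle what follows. On data collection: "Participants who have received the intervention will complete follow-up assessments". On analysis: "No efficacy analyses will be performed for withdrawn cases".

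The Emergency unblinding section adds a further ground, a list of severe events after stimulation: "Participants meeting these criteria will be immediately withdrawn from the trial". It does not say whether their PONV outcome is still collected.

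The Statistical analysis section describes the test, the margin and the confidence interval, but names no analysis population that would override the exclusion. Under The principle of randomness the acupuncturist opens the allocation envelope, and under Blind method that same person alone inserts and removes the needles.

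**The concern.** Randomisation protects a comparison of the groups as randomised. Here membership of the analysis set is decided later, inside the same 24 h window in which the primary outcome occurs. Three routes could make the exclusions differ between arms:

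- **Site.** The penetrating needle is at PC6 near the wrist in group A and higher on the forearm in group B, so intolerance could differ.
- **Outcome.** A nauseated or retching patient may want the devices off, and would then leave the analysis because of the event being counted.
- **Knowledge of allocation.** The removal that triggers exclusion is performed by someone who knows the group.

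The stated aim is to verify the added benefit of acupoint stimulation over routine prophylaxis. A comparison restricted to people who kept the devices for 24 h answers a narrower question. For withdrawn participants who were treated and followed up, no missing-data problem forces the exclusion. An unseen analysis plan could not restore these participants without contradicting the protocol's own sentence.

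**Working it through.** **1. The plan's own figure.** Inputs from Sample size estimation: p1 = 0.610 ("PONV incidence in the control group is estimated to be 61"%), p2 = 0.610 × 0.7 = 0.427, one-sided α = 0.05 (Z = 1.645), power 0.8 (Z = 0.84).

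- Mean rate = (0.610 + 0.427)/2 = 0.5185.
- First term: 1.645 × √(2 × 0.5185 × 0.4815) = 1.1624.
- Second term: 0.84 × √(0.2379 + 0.2447) = 0.5835.
- n = (1.1624 + 0.5835)² / 0.183² = 91.02, so 92 per group, as stated.
- 92/0.9 = 102.2, so 103, or 104 when rounded to an even number for blocks of 4, as stated.

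Other sections give 216 in total (108 per arm), so results below use 104 or 108 as marked.

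**2. Bias from exclusion when the needles do nothing.** The true rate is 0.61 in both arms. If a share w of an arm is dropped and their PONV rate is r, the remaining rate is (0.61 − w·r)/(1 − w). The values of w and r are assumptions, because the documents give none for withdrawn cases; w = 10% equals the attrition allowance. Rejection is for a plain one-sided 5% Z-test of no difference, Φ((rate B − rate A)/SE − 1.645), with 104 per arm randomised and the same share dropped in each arm.

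| Dropped per arm | PONV in A's dropouts | PONV in B's dropouts | A after exclusion | B after exclusion | Bias (A − B) | Rejection |
|---|---|---|---|---|---|---|
| 10% | 61% | 61% | 61.0% | 61.0% | 0 | 5.0% |
| 10% | 85% | 85% | 58.3% | 58.3% | 0 | 5.0% |
| 5% | 85% | 61% | 59.7% | 61.0% | −1.3 points | 7.2% |
| 10% | 85% | 61% | 58.3% | 61.0% | −2.7 points | 10.1% |
| 15% | 85% | 61% | 56.8% | 61.0% | −4.2 points | 14.2% |
| 10% | 37% | 61% | 63.7% | 61.0% | +2.7 points | 2.2% |

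Fourth row in full: (0.61 − 0.10 × 0.85)/0.90 = 0.5833. With 93.6 left per arm, SE = √((0.5833 × 0.4167 + 0.61 × 0.39)/93.6) = 0.0717. Φ(0.0267/0.0717 − 1.645) = Φ(−1.27) = 0.10. At 108 per arm it is 10.3%.

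**3. Link to the margin rule.** The Statistical analysis section also judges superiority by a 97.5% one-sided limit against 0.183. If the upper limit must lie below −0.183, false positives stay under 0.01% in every row. If it need only lie below +0.183, as literally written, the criterion is met with no effect and no exclusions about 77% of the time: SE = √(2 × 0.2379/104) = 0.0676, and Φ(0.183/0.0676 − 1.96) = Φ(0.75). In the fourth row it is met about 83% of the time. The rejection column therefore describes neither reading of that rule.

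**4. Power if everyone is analysed as assigned.** Assume a share f of group A gains nothing (rate 0.61) and every outcome is available. The rate in A is then (1 − f) × 0.427 + f × 0.61.

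| f | Difference | Power, 104 per arm | Power, 108 per arm |
|---|---|---|---|
| 0 | 18.3 points | 84.5% | 85.6% |
| 5% | 17.4 points | 81.0% | 82.3% |
| 10% | 16.5 points | 77.2% | 78.5% |
| 15% | 15.6 points | 72.9% | 74.3% |

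**5. Which removals are premature.** Devices are applied before induction. Blind method has them removed 24 h post-intervention; the Abstract and the Intervention section keep them in place until 24 h after surgery. If the 24 h in the withdrawal rule runs from the end of surgery, removal on the Blind method schedule would itself count as premature. The excluded set is not defined until these sections agree.

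**The case against.** The strongest reply is that exclusions may well be balanced. On each forearm both arms wear one real and one identical-looking sham device, no De Qi is sought, and the Discussion describes minimal discomfort with indwelling periods of up to 72 h. If removals match in frequency and prognosis, the bias is zero. If few are dropped, it is small: 5% gives about 7% rejection even with the unfavourable asymmetry. This stands as a limit on size. It does not rescue the rule, because balance cannot be known in advance.

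Four stronger readings are tempting, and the documents do not support them:

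- *The rule favours acupuncture.* It may do so, but the reverse asymmetry works against it. Nothing in the documents fixes the direction.
- *The outcomes of emergency-unblinded participants are collected and then discarded.* Their exclusion follows from reading the two sections together. Their follow-up rests only on the general follow-up sentence under Eligibility criteria; the emergency section does not state it, and some such patients may not be assessable.
- *Deliberate hypotension during surgery will trigger emergency withdrawals.* That needs a pulse pressure the documents do not give. Controlled hypotension also applies to both arms, so no difference between them is shown.
- *The trial's error rate is 10% or 15%.* Those figures belong to a plain no-difference test under assumed exclusions, not to the margin rule.

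The reply is also right that including everyone costs power, as step 4 shows.

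**Conclusion.** The concern holds in this form. The protocol explicitly makes an analysis conditioned on post-randomisation events its only efficacy analysis, while continuing to follow up participants who received the intervention. This is a stated rule, not a detail left to an analysis plan.

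Its effect cannot be sized from the documents. Under the assumptions shown, with 10% dropped per arm, the bias runs from −2.7 through zero to +2.7 points, and the plain one-sided 5% test rejects between about 2% and about 10% of the time. These figures rest on assumed PONV rates of 85% or 37% in one arm's dropouts and a true rate of 61% in both arms. What is certain is that the protection of randomisation is given up for no stated reason. The rule should be changed before outcomes are seen.

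**What to change.** Replace the exclusion sentence under Eligibility criteria with the following, and align Emergency unblinding and Statistical analysis with it:

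> The primary efficacy analysis includes all randomised participants who had the devices applied and underwent surgery, in their assigned group, whatever the time or reason of device removal, intolerance, conversion to single-jaw surgery or unblinding, using the outcomes collected. Only participants whose surgery was cancelled, and who therefore have no postoperative outcome, are left out. Unassessable outcomes are treated as missing data. The analysis without withdrawn cases is a sensitivity analysis.

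Emergency unblinding should also say whether follow-up of the primary outcome continues where it is possible. The Abstract, Blind method and Intervention sections must be reconciled on whether 24 h runs from application or from the end of surgery, because this defines the completer set for the sensitivity analysis.

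The cost is edits to a few sections and, for most participants concerned, no new data. Early removals may dilute the effect: if 10% of group A gained nothing, one-sided power is about 77% at 104 per arm or 78.5% at 108, against the planned 80%.

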### The principle of randomness

This study will utilize computer-generated block randomization with a total sample size of 216 cases divided into 54 blocks, each containing 4 cases. These blocks are equally allocated to two groups, with sequences randomly arranged within each block. Allocation details will be secured in opaque, sealed envelopes. After obtaining signed informed consent, the acupuncturist administering the intervention will access the randomization sequence through the Random.org website (https://www.random.org/) and then open the corresponding sealed envelope to access group assignment details.

### Blind method

This trial employs a sham-controlled design. The true stimulation group receives intervention at the PC6 acupoint, while the sham stimulation group undergoes stimulation at a non-acupoint site on the forearm. A designated acupuncturist performs thumb-tack needle insertion at predetermined locations according to group assignment, followed by application of an opaque white sterile patch to secure the device and maintain blinding. The same practitioner removes all thumb-tack needles 24 h post-intervention. Both needle insertion and removal procedures are exclusively performed by the assigned acupuncturist. A trained follow-up coordinator conducts postoperative assessments.

To assess the integrity of participant blinding, within 24 h postoperatively, participants will be asked to guess whether the stimulation was received at a real acupoint (PC6) or at a sham acupoint (non-acupoint). Responses will be recorded on the case report form (CRF), and the proportion of correct guesses will be summarized.

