### Intervention

Upon entering the operating room, the acupuncturist generates a randomization sequence via the Random.org website (https://www.random.org/) to access the corresponding sealed envelope containing group allocation details. Before induction of anesthesia, the acupuncturist applies the assigned thumb-tack devices bilaterally according to the randomized allocation. Both groups receive two thumb-tack devices: a real needle (0.25 mm × 2.0 mm, disposable sterile press needles) and a sham needle with identical appearance but no needle tip. In Group A, the real device is bilaterally applied to the PC6 acupoint – located three finger breadths proximal to the wrist crease between the palmaris longus and flexor carpi radialis tendons – while the sham device is bilaterally positioned at the non-acupoint site six finger breadths proximal to the wrist crease and 2 cm ulnarly. Group B receives the inverse configuration, with sham stimulation bilaterally at PC6 and real stimulation bilaterally at the non-acupoint site. The sham site maintains a 3 cm radius free of established acupoints to prevent collateral stimulation (Figure 3). No deliberate De Qi sensation is elicited during application. Opaque sterile patches will be applied to both intervention sites to conceal the allocation information (Figure 4), with devices remaining *in situ* for 24 postoperative hours. All acupuncture-related procedures are performed in strict accordance with aseptic principles to minimize the risk of infection. Both groups receive standardized PONV prophylaxis per guidelines (18): dexamethasone 5 mg, palonosetron 0.075 mg, propofol target-controlled infusion (TCI) 0.5 μg/mL, and pharyngeal packing.

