### Data collection and outcome assessment

Following informed consent acquisition, research staff will document baseline parameters including gender, age, height, body weight, body mass index (BMI), history of motion sickness, smoking status, ASA classification, and Apfel risk score (6). Perioperative records will encompass surgical duration, intraoperative fluid balance, controlled hypotension period (defined as MAP <65 mmHg), extubation latency (time from surgery completion to tracheal tube removal), and cumulative dosages of anesthetic agents (propofol, sufentanil, remifentanil).

A designated and trained clinical research specialist will conduct follow-up assessments twice daily (08:00–10:00 and 18:00–20:00) during the initial 24 postoperative hours, evaluating PONV severity, pain intensity, and adverse events. The 12-point PONV assessment scale documents the worst nausea episode per evaluation window, in which 0 = no nausea, 10 = most severe nausea, and 11 = retching/vomiting.

The primary outcome measure of this study is the 24-h incidence of any episode of nausea, vomiting (retching or vomiting) or both (i.e., postoperative nausea and vomiting) postoperatively. PONV is defined as the PONV score ≥1.

Secondary outcomes include: (1) stratified PONV incidence at 0–2 h, 2–6 h, and 6–24 h intervals; (2) peak PONV severity scores during these timeframes; (3) 24-h postoperative QOR-15 score to assess the recovery of patients; (4) the total number of patient-controlled analgesia pump pressed by the patient within 24 h; (5) overall NRS pain score within 24 h; (6) postoperative hospital length of stay; (7) the consumption of tramadol and droperidol.

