The intradermal needle, a thumb-tack shaped medical device, is subcutaneously implanted to deliver sustained acupoint stimulation through localized mechanical activation. This modality provides continuous regulation of meridian function and qi-blood balance through controlled dermal neuromodulation (36, 37). Clinical evidence supports extended indwelling periods (up to 72 h) with minimal discomfort and unrestricted patient mobility, contributing to its widespread adoption in contemporary practice (38–40). The superficial anatomical placement of PC6 allows precise needle insertion using microfilament devices, effectively avoiding trauma to critical neurovascular structures including the median nerve and radial artery in the wrist region.

To optimize blinding integrity, a forearm region devoid of established acupoints within a 3 cm radius is selected as the sham stimulation site. Participants in the sham group receive superficial dermal stimulation mimicking needle insertion trauma using identical sterile devices. Opaque surgical dressings are symmetrically applied to all intervention sites to preserve allocation concealment. This protocol ensures triple blinding: neither participants, anesthesiologists, nor outcome assessors can visually or tactilely discern active versus sham needle placement.

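### The Blind method section times needle removal from placement, so patches can come off about 3 h or more before the 24-h postoperative outcomes; no section puts the final patient-reported assessments first

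*Protocol article*

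**What the plan says.** The protocol article times removal in four places, with different clocks.

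- **Blind method:** "The same practitioner removes all thumb-tack needles 24 h post-intervention".
- **Intervention:** the devices stay in place "for 24 postoperative hours".
- **Abstract, Methods:** "The needles will remain in place up to 24 h postoperatively at least".
- **Eligibility criteria:** one ground for withdrawal is "premature removal (<24 h) of thumb-tack needles for any reason", with no starting point for the 24 h.

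The intervention itself is timed clearly: "Before induction of anesthesia, the acupuncturist applies the assigned thumb-tack devices bilaterally according to the randomized allocation". The Intervention column of Table 1 is also headed as before induction.

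The outcomes run on the postoperative clock. The primary outcome is any PONV score of 1 or more over 24 h after surgery, on a 12-point scale (0 to 11). A secondary outcome is the "24-h postoperative QOR-15 score to assess the recovery of patients". The blinding guess is asked within 24 h after surgery. The coordinator visits at two fixed clock windows, 08:00–10:00 and 18:00–20:00, during the first 24 postoperative hours.

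Each participant has both kinds of device. The sham is described as "a sham needle with identical appearance but no needle tip", and opaque patches over both sites conceal the allocation. The Discussion claims that "neither participants, anesthesiologists, nor outcome assessors can visually or tactilely discern active versus sham needle placement".

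**The concern.** Participant blinding rests on the patches. The two devices differ only in the tip, so which site carried the tip is the allocation. Once the patches are lifted, a participant may be able to see which device had a point or which site has a puncture mark. Consenting participants have been informed about the protocol, and the guess question itself contrasts PC6 with a non-acupoint.

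The primary outcome is self-reported and has the lowest possible threshold, a score of 1. QoR-15 is also self-reported. Answers given after a participant has learned the allocation are in effect open-label. A guess recorded then says little about whether blinding held during the trial. The Limitations section calls blinding the main methodological challenge and accepts a possible loss of efficacy to protect it, so an avoidable gap in the last hours deserves closing.

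**Working it through.** The plan gives no figure for the gap between removal and the outcome time point, so there is nothing to reproduce. It follows from clock arithmetic.

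**Inputs**
- Removal under Blind method: 24 h after the intervention.
- Start of that clock: before induction (Intervention; Table 1).
- End of the PONV window and nominal time of QoR-15: 24 h after surgery (Data collection and outcome assessment).
- Cues to length of surgery: a second antibiotic dose 3 h into the operation (Anesthetic management) and a subgroup cut at 200 min (Statistical analysis). These are cues only and leave out the time from placement to incision.
- Assumed longer intervals from placement to end of surgery: 300 and 420 min.

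**Formula.** Let L be the time from needle placement to the end of surgery. Removal in postoperative hours = 24 − L. The part of the 24-h window after removal = L/24.

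| L | Removal at postoperative hour | Window after removal |
|---|---|---|
| 180 min (3 h redosing cue) | 24 − 3.0 = 21.0 | 3.0/24 = 12.5% |
| 200 min (subgroup cut) | 24 − 3.33 = 20.7 | 3.33/24 = 13.9% |
| 300 min (assumed) | 24 − 5.0 = 19.0 | 5.0/24 = 20.8% |
| 420 min (assumed) | 24 − 7.0 = 17.0 | 7.0/24 = 29.2% |

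**Effect of the fixed visits (assumed clock times).** Take placement at 08:00 and surgery ending at 13:00. Blind method puts removal at 08:00 next day, and the 24-h point is 13:00. The 08:00–10:00 visit, the last fixed visit inside the window, then falls at or after removal. It reports the worst nausea since the previous evening's visit, a recall period of 12 to 16 h (20:00 to 08:00, up to 18:00 to 10:00). With placement at 09:00, that visit window lies partly after removal. With placement from 10:00 to 13:00 and L up to 5 h, no fixed visit falls between removal and hour 24, but a QoR-15 taken at 24 h still follows removal.

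**The other clock.** Under the Abstract and Intervention wording, the gap at hour 24 is 24 − 24 = 0 h. Removal and the 24-h QoR-15 share a nominal time. The acupuncturist removes the devices and the coordinator assesses, and no section says who goes first. Table 1 ticks stimulation and QoR-15 in the same 6–24 h column and schedules neither removal nor the guess.

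**The case against.** The strongest reply is that most of the document points the other way. The Abstract and Intervention sections keep the devices on to 24 h after surgery, Table 1 shows stimulation through the 6–24 h column, visits are confined to the first 24 postoperative hours, and the guess is asked within that period. Read together, these put nearly everything before removal, and the gap of hours arises only from the Blind method clock. This stands: if the sections are reconciled to the postoperative clock, only the tie at hour 24 remains. It does not dispose of the point, because the Blind method rule is stated, names who acts and when, and could be followed as written.

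A second reply is that unblinding at removal is inferred. No section says that participants see the underside of the device or can read a 0.25 mm puncture, and they would also need to know which site is PC6. This stands too. Equally, no section says that removal is shielded from view.

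A third reply is that bedside order is operational detail for the full protocol, and the flow figure is not shown. That would answer a mere silence. It does not answer a stated removal time that precedes the outcomes.

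Some stronger readings are tempting but unsupported:
- A reader might infer that outcomes follow unblinding under either removal time. Under the postoperative clock there is only a tie.
- A reader might count hours from removal to the next visit after hour 24. The protocol schedules no such visit.
- A reader might think that participants whose needles come off early bring unblinded reports into the efficacy results. The Eligibility criteria withdraw them and exclude them from efficacy analyses.
- A reader might express the bias as a share of the planned 18.3-point difference. No figure in the documents supports any particular shift in reporting.

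**Conclusion.** The point holds in a limited form. As the Blind method section is written, devices and patches come off about 3 h before the 24-h postoperative point on the protocol's own cues, and up to 7 h before it if longer intervals are assumed. This reads the 24 h as running from needle placement, which Table 1 supports. The last part of the PONV window, a QoR-15 taken at 24 h and possibly the guess can then be collected after the patches are lifted. The guess may also be asked earlier, and not every participant's last visit is affected.

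Whether participants would learn their allocation is a reasonable inference, not a stated fact. The size of any bias cannot be derived. The primary endpoint counts any episode, so late knowledge could change the result only for participants with no episode yet recorded. No sample-size figure is affected. The Discussion's assurance on blinding is not secured once the patches are off. The gap should be closed, because the stated rule permits it and the correction is small.

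**What to change.** 1. Reconcile the removal time across the Abstract, Eligibility criteria, Blind method and Intervention sections, with one stated starting point for the 24 h. Which time to keep is for the trial team; this review does not propose one.
2. Whichever time is kept, add to Blind method and Intervention that the coordinator completes the final PONV score, QoR-15 and blinding guess with the patches intact, and that the acupuncturist lifts the patches only afterwards.
3. Record the times of the final assessment and of removal on the CRF, so that the order can be verified for each participant.

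Beyond the reconciliation, the cost is one sentence of procedure and two CRF time fields, with existing staff. The small downside is that the acupuncturist and the coordinator must agree the order on the second day.
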